### Study design

This study will be a pilot pragmatic parallel-group dyadic randomized controlled trial (RCT) comparing a shared book reading intervention (young people with DS paired with university student partners) to a minimal-activity control group.

All individuals with DS recruited into the study will be randomly paired with a university student to form a dyad. Depending on recruitment numbers, if more university students are enrolled than young people with DS, some dyads may consist of one participant with DS and two students (i.e., a 1:2 pairing). Each dyad will be randomized 1:1 to either the intervention group or the control group. Recruitment will take place over a 12-month period, with each participant involved in their assigned condition for 8 weeks. After this period, participants in the control group will also be offered the intervention. The primary outcome will be assessed at 8 weeks post- randomization. An extended phase will allow for exploration of long-term effects and sustainability, with outcomes measured at 6 and 12 months to inform future trial design.

### Setting

Young people with DS will be recruited from community settings in Macau in close collaboration with the MDSA. University students will be recruited from universities in Macau.

### Participants

Inclusion criteria for participants with DS are as follows: (1) diagnosis of DS; (2) aged 10–20 years; (3) ability to participate in the intervention and assessments either independently or with caregiver support. Potential participants will be approached through DS community centers and social media advertisements. The age range was selected based on discussion and agreement with the PPI group, which included members of the Macau Down Syndrome Association with experience organizing social activities for this population. Based on their prior experience, the 10–20 years are group was deemed most appropriate.

The inclusion criteria for university student participants are as follows: (1) age 18 years or older; (2) ability to read and understand books in English or Chinese; (3) ability to communicate in English, Mandarin, or Cantonese; (4) absence of severe visual or reading impairments that would affect reading ability. Exclusion criteria include: current hospitalization; severe comorbidities (e.g., uncontrolled epilepsy) or inability to participate even with caregiver support; inability to participate due to severe visual or speech impairments without an available caregiver to assist); or concurrent participation in another clinical study that could interfere with this intervention or its assessments.

While the age range for participants with DS is broad, the intervention focuses on fostering mentorship and social connection. The university students will act as supportive partners, adapting their engagement strategies to the developmental level of their assigned participant. All participants (or their legal guardians, for participants with DS) will provide informed consent after a full explanation of the study procedures, time commitment, and their rights (including the voluntary nature of participation and the right to withdraw at any time). We will ensure they have ample time to ask questions and consider participation before signing the consent form. For participants with DS who are minors or require guardian support, consent will be obtained from their caregivers (legal representatives) in addition to assent from the participant. We will use easy-to-understand language and visual aids to explain the study to ensure that participants with DS and their caregivers fully understand the study's purpose, procedures, and potention risks. All participants will be given sufficient time to consider participation. Young people with DS and university student participants in both groups will receive a shopping voucher worth 160MOP (approximately $20USD) upon completion of the 8-week follow-up assessment.

### Forming dyads

We will randomly pair each young person with DS with at least one university student to form dyads and facilitate shared reading experiences. This pairing is designed to encourage social connection and friendship development between the partners.

### Randomization and allocation

Participants within their dyads will be randomized (1:1) to either the intervention or control group. A computer-generated randomization list (using random block sizes of 2 and 4) will be prepared at the University of Macau, and allocation will occur after baseline data collection. An external statistician not involved in the study will perform the allocation centrally using this list. Researchers conducting the baseline and follow-up assessments will be blinded to group allocation.

### Shared book reading intervention

The shared book reading intervention will be led by an intervention leader, a doctoral research student who is a registered nurse. The intervention leader will be assisted by facilitators who will receive 1-h training in DS-adapted communication strategies (e.g., visual supports, paced questioning) and engagement techniques (e.g., dialogic reading, sensory accommodations). Sessions will comprise: (i) a 10-min icebreaker involving a musical chairs adaptation (flower-passing with music, followed by sharing a favorite word from previous sessions) and facial expression imitation games to build rapport; (ii) a 30-min shared reading using PPI-approved books, with adaptations for non-verbal participants (yes/no questions) and attention challenges (10-min reading blocks with stretch breaks); and (iii) a 10-min reflection using visual prompts (emoji cards for “favorite part” discussions) and icon-based logbook entries. This training will be delivered by the intervention leader. Weekly facilitator reports will document implementation challenges (e.g., participant disengagement) for iterative problem-solving.

Facilitators will maintain participant's engagement, and caregivers of young people with DS are welcome to attend. To minimize bias, facilitators will follow a standardized manual (Supplementary File 1: Intervention Facilitator Manual). Session fidelity across all dyads will be assessed using checklists (Supplementary File 2: Fidelity Checklist and Scoring Criteria) completed by the intervention leader. Each session will conclude with a brief reflection period during which participants discuss what they have read and plan for the next session. Weekly reminders will be sent to families and students regarding session times. Attendance will be incentivized through a sticker system, with participants collecting stickers in a provided scrapbook.

As suggested during PPI meetings, we will introduce a “Growth Record” logbook (Supplementary File 3: Participant Growth Logbook Template) for each participant with DS. This personal logbook allows the young people (with caregiver assistance as needed) to record each session's reading activities—such as books read, new vocabulary, and personal reflections or progress. Caregivers are encouraged to help maintain the log, which supports tracking the child's development and sustains engagement with the intervention at home. The logbook is optional and adaptable for all ages. Caregivers will receive guidance on supporting home reading activities, though no formal home practice is required. The growth log also serves as a bridge between the child, family, and student volunteer, enabling sharing of entries or achievements to foster communication and a sense of accomplishment. Families are encouraged to continue using the log after the study to support sustained reading habits. This logbook concept emerged from PPI feedback aimed at enhancing participant engagement.

### Control group

Participants in the waitlist control group will be informed that they must wait 8 weeks before beginning the shared book reading sessions. Dyads in the control group will not be introduced during this 8-week period; participants with DS and students in this arm will only meet after the 8-week follow-up, when the intervention begins. To maintain engagement among youth with DS in the control group, they will be provided with three books to read independently or with their family during the waiting period. After the 8-week wait, control group participants will be invited to join the shared reading sessions. At that point, each young people with DS in the control group will be introduced to their student partner and may then participate fully in the weekly sessions. This approach ensures that while the control group receives books, they do not engage in dyadic shared reading until after the 8-week waitlist period. This design is methodologically critical, aligns with PPI group consensus that all participants eventually receive the intervention, and fulfills ethical requirements.

### Outcome measures

Outcome measures will be collected at baseline (T0) and 8 weeks post-randomization (T1) for both the intervention and control groups. Following the initial 8-week RCT phase, all participants (including those from the waitlist control group) will receive the intervention; additional follow-ups will be conducted at 6 months (T2) and 12 months (T3) post-randomization in this single-arm extension phase. For the intervention group, outcomes for participants with DS will be collected at the end of the final session through researcher-administered interviews. For the control group, 8-week outcomes for participants with DS will be collected via researcher-conducted telephone interviews. University student participants in both groups will complete their outcome measures through an online survey, with reminder prompts sent after 1 and 2 days if not completed.

At T1, dyads in the intervention group will complete one additional measure (assessing the dyad's overall friendship) that will not be administered to the waitlist control group; all other outcome measurements are identical for both groups. The primary outcome of this study is the health-related quality of life of young people with DS at 8 weeks (T1), measured using the Pediatric Quality of Life Inventory (PedsQL)4.0. Secondary outcomes include the mental wellbeing of the student partners (assessed using the EPOCH scale) and the quality of the friendship within the dyad (assessed via the Friendship Quality Questionnaire, FQQ). Additionally, caregivers of participants with DS will complete a Global Perceived Effect (GPE) scale to evaluate their perception of change in the quality of life of the participant with DS.

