**Methods:**

This study is an 8-week pilot dyadic randomized controlled trial (RCT) comparing a shared book reading intervention to a minimal activity control. The study will then continue for 12 months as a single-arm cohort study. Young people with DS and university students will be recruited, formed into dyads, and then randomized to either the intervention or control group. The intervention involves pairing a young person with DS with a university student for a weekly, 1-h shared book reading session. The control group will be provided with three books to read at their leisure over the 8 weeks. The primary outcome is the health-related quality of life of young people with DS, measured using the Pediatric Quality of Life Inventory (PedsQL 4.0). Secondary outcomes include the Engagement, Perseverance, Optimism, Connectedness, and Happiness (EPOCH) scale for measuring wellbeing. The Friendship Quality Questionnaire (FQQ) will be used to measure the dyad's level of friendship in the intervention group at 8 weeks. Measurements will be taken at baseline (T0) and at 8 weeks (T1). After 8 weeks, all participants will be offered the opportunity to continue in the study, joining the weekly shared book reading intervention; outcome measures will then be assessed at 6-month (T2) and 12-month (T3) follow-ups. Mixed linear regression models will be used to compare the intervention and control groups at 8 weeks. For the 6-month and 12-month follow-ups, change scores from baseline will be analyzed to test for potential long-term effect.

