### Statistical analysis

A target sample size of 12 dyads (12 per group) was selected to provide preliminary estimates of variability and feasibility, consistent with recommendations for pilot trials (26, 27), while remaining pragmatic given resource constraints in DS population studies. Statistical analysis will be performed by a researcher blinded to group allocation, and an independent statistician will verify the primary outcome analysis. The primary analysis will compare the shared book reading intervention group and the waitlist control group for the primary outcome at 8 weeks post-randomization. Secondary analysis will include analysis of secondary outcomes at 8 weeks post-randomization. Additionally, we will use an actor–partner interdependence model (APIM) to explore within-dyad relationships (examining how one member's baseline quality of life or mental wellbeing might influence both their own and their partner's outcomes). Dyad composition and potential differences in interpersonal dynamics will be accounted for within the APIM. For outcome comparisons, we will use mixed-effects linear models to account for repeated measures and dyad clustering, and results will be presented as mean differences between groups with 95% confidence intervals. Models will adjust for baseline scores in outcomes and covariates, including age, sex, and education level.

The primary analysis will be conducted using an intention-to-treat (ITT) approach. Secondary analyses will be performed after imputation of missing data. A sensitivity analysis will be conducted using multiple imputations for missing data (including all secondary outcomes and covariates in the imputation model). All analyses will be performed using R in RStudio (28).

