Feasibility of the RCT will be evaluated based on participant adherence to the intervention and completion rates of outcome measures at each time point. Acceptability of the intervention will be assessed through qualitative feedback from participants in the intervention arm. Caregiver presence and group size will be documented and analyzed as potential moderators of intervention effects. We will maintain continuous consultation with the PPI panel throughout the study to gain insights into intervention implementation. This ongoing feedback will help researchers understand factors that encourage or discourage participation, improving study processes for consideration in future studies. We will also involve the PPI panel in disseminating findings, incorporating their input when presenting results to local stakeholders.

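### For participants with DS, the stated 8-week collection point depends on attending the last reading session in the intervention arm but on no session in the control arm, and it has two unreconciled time anchors

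*Protocol article*

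**What the plan says.** Under Outcome measures, the protocol article first gives one time point for everyone: "Outcome measures will be collected at baseline (T0) and 8 weeks post-randomization (T1) for both the intervention and control groups". Study design agrees: "The primary outcome will be assessed at 8 weeks post- randomization". The same Outcome measures paragraph then gives participants with DS a separate collection point in each arm:

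- Intervention: "For the intervention group, outcomes for participants with DS will be collected at the end of the final session through researcher-administered interviews".
- Control: "For the control group, 8-week outcomes for participants with DS will be collected via researcher-conducted telephone interviews".

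Students in both arms answer an online survey with reminders.

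Under Statistical analysis, "The primary analysis will be conducted using an intention-to-treat (ITT) approach", and multiple imputation is a sensitivity analysis. Feasibility is judged on adherence and on "completion rates of outcome measures at each time point". The limitations section expects difficulty with retention. The article states no attendance or dropout rate, no SD for PedsQL, and no visit window.

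**The concern.** Intention-to-treat needs an outcome sought from every randomized participant in the same way, whatever they did after randomization. Here the stated opportunity to be measured follows randomization in one arm and continued participation in the other. A young person who has stopped attending, or is away on the last day, has no stated T1 contact in the intervention arm. The comparable control has one.

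Absence may be linked to how the young person is doing. The article itself names lack of motivation and difficulty keeping focus as common barriers, and facilitators are to report disengagement. If the link exists, the observed intervention mean is selected and the control mean is not.

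Two products of the pilot are at stake. One is the effect estimate, which the Discussion says will inform the sample size of the definitive trial. The other is the follow-up rate: for participants with DS in the intervention arm, a missed last session would also count as a missed T1.

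**Working it through.** The plan has no figure of its own to reproduce here. The check compares the two rules and then shows what they could do under stated assumptions.

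**1. The rules side by side (participants with DS)**

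| | Intervention | Control |
|---|---|---|
| Nominal T1 | 8 weeks post-randomization | 8 weeks post-randomization |
| Stated contact | end of final session | telephone interview |
| Contact requires attendance | yes | no |
| Stated route for a non-attender | none | not needed |

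**2. Timing**

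Sessions are weekly (Abstract, Methods). Assume eight of them, the first *d* days after randomization, with *c* weeks cancelled. The last session falls on day *d* + 7 × 7 + 7*c* = *d* + 49 + 7*c*. Eight weeks is day 56, so the two anchors agree only if *d* + 7*c* = 7.

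- *d* = 0, *c* = 0: day 49 (week 7)
- *d* = 7, *c* = 0: day 56 (week 8)
- *d* = 14, *c* = 0: day 63 (week 9)
- *d* = 28, *c* = 0: day 77 (week 11)

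The article gives neither *d* nor *c*. Starting within two weeks of randomization with no cancellation keeps the last session within 7 days of day 56.

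**3. Chance of losing a primary outcome**

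Let *q* be the share absent from the last session (assumed) and *n* the number per arm. The sample size reads as 12 dyads and also as 12 per group, so both *n* = 12 and *n* = 6 are shown. P(at least one lost) = 1 − (1 − *q*)^*n*. The standard error of the group difference, in SD units, is √(1/*n* + 1/(*n*(1 − *q*))), with controls complete.

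| *q* | *n* = 12: P, SE | *n* = 6: P, SE |
|---|---|---|
| 0% | 0, 0.408 | 0, 0.577 |
| 10% | 0.72, 0.419 | 0.47, 0.593 |
| 20% | 0.93, 0.433 | 0.74, 0.612 |
| 30% | 0.99, 0.450 | 0.88, 0.636 |

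**4. Possible bias**

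Use a normal selection model in which the propensity to attend has correlation ρ with the T1 score (assumed). The observed intervention mean is shifted by ρ × φ(z_q)/(1 − *q*) SD, where φ is the normal density and z_q the *q* quantile. For *q* = 0.2, φ(0.842) = 0.280 and 0.280/0.8 = 0.350, so ρ = 0.3 gives 0.105 SD and ρ = 0.5 gives 0.175 SD.

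| *q* | ρ = 0 | ρ = 0.3 | ρ = 0.5 |
|---|---|---|---|
| 10% | 0 | 0.058 | 0.097 |
| 20% | 0 | 0.105 | 0.175 |
| 30% | 0 | 0.149 | 0.248 |

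A negative ρ would reverse the sign.

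**The case against.** The best defense is that this is an article condensing a fuller protocol. It names the planned route and never says that non-attenders go unmeasured. Table 1 lists PedsQL at T1 for both groups without an attendance condition, and the trial coordinator keeps in touch with families throughout, though for adverse events. Nor does the article promise that every control will be reached. Missing data are anticipated through multiple imputation, and the authors say that differences will be read cautiously.

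Much of this stands, and it rules out four stronger readings that a reader might infer:

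- *Non-attenders will have no T1 value, so the comparison is attenders against all controls.* The text supports only that no other route is stated; the full protocol may hold a fallback.
- *T1 in the intervention arm is not at 8 weeks.* Two statements put it there. With weekly sessions over an 8-week period the last one nominally falls around week 7 or 8, and no start delay is documented.
- *Adherence and outcome completion become one measure.* Adherence covers all sessions, and completion covers other time points and the students. The overlap is confined to last-session attendance and T1 completion among intervention participants with DS.
- *All intervention-arm outcomes are affected.* The student surveys are not.

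The defense does not remove the core. The arm-specific collection point is written down, in a paragraph detailed enough to give the days on which students are reminded. Imputation is a poor substitute for values that a telephone call could obtain, and attendance is not among the variables named for the imputation model.

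**Conclusion.** The point holds as a weakness in a stated collection rule. Followed as written, the rule makes T1 for participants with DS depend on last-session attendance in the intervention arm only, and it leaves two anchors for T1 that must be reconciled.

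The documents do not settle the size or direction of any bias. It is zero if absence is unrelated to outcome. It is about 0.06 to 0.25 SD toward benefit for 10% to 30% absence and a correlation of 0.3 to 0.5, all of which are assumptions. That is smaller than the standard error of the pilot (0.408 SD with 12 per arm, 0.577 SD with 6). Unlike sampling error, however, it would not shrink with more participants, and it would pass into the planning of the next trial.

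The feasibility consequence needs no assumed correlation: as written, a missed last session and a missed T1 are the same event for these participants. The change is worth making before T1 data are collected, because values not sought then cannot be recovered.

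**What to change.** In Outcome measures, replace the two arm-specific sentences for participants with DS by one rule, for example:

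> *T1 is assessed in every randomized participant with DS, in both arms, by researcher telephone interview on day 56 after randomization (± 7 days), regardless of session attendance or discontinuation of sessions.*

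Under Statistical analysis, add that T1 completion is reported by arm and separately from session attendance. If the full protocol already has a route for non-attenders, the article should state it.

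The mode should be the same for all. Telephoning only the absentees would tie interview mode to attendance within the intervention arm and keep the difference in mode between arms.

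The cost is small: up to 12 extra calls (6 if the total is 12 dyads) by a procedure already planned for controls, and loss of the interview at the session in the intervention arm. For some dyads T1 will fall shortly before or after the last session, and a dyad that starts late may not have finished its sessions by T1. The rule removes missingness caused by the collection point itself; ordinary non-response can still occur in either arm.

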However, several limitations should be acknowledged. First, the use of a waitlist control design, rather than an active concurrent control, may introduce potential bias, as control group participants will eventually receive the intervention. This design also raises the possibility of contamination, as control group participants may have access to books and opportunities to engage in shared reading with others outside the study. Second, blinding of participants to their group allocation (intervention or control) is not feasible, which may lead to differing expectations of improvement and influence outcomes during data collection. Finally, challenges related to recruitment and participant retention are anticipated, which could impact the study's overall feasibility and generalizability. As a pilot study, the sample size is limited, and the study may be underpowered to detect modest intervention effects. Consequently, any outcome differences will be interpreted cautiously and primarily used to inform the design of a larger trial. Despite these limitations, this pilot study represents an important first step in evaluating an innovative intervention. The insights gained will be invaluable for planning a definitive trial and could open new avenues for mental wellbeing promotion in young people with developmental disabilities (36).

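### At 8 weeks the primary outcome is taken at the last reading session in one arm and by telephone in the other, so assessor blinding fails and mode of assessment cannot be separated from treatment

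*Protocol article*

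**What the plan says.** The protocol article, Outcome measures, makes PedsQL 4.0 in young people with Down syndrome at 8 weeks after randomisation (T1) the primary outcome. It then sets a different collection route for each arm:

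- Intervention: "For the intervention group, outcomes for participants with DS will be collected at the end of the final session through researcher-administered interviews".
- Control: "For the control group, 8-week outcomes for participants with DS will be collected via researcher-conducted telephone interviews".

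The same section says of everything except the friendship questionnaire that "all other outcome measurements are identical for both groups". University students are handled alike in both arms: "University student participants in both groups will complete their outcome measures through an online survey".

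Under Randomization and allocation the article states: "Researchers conducting the baseline and follow-up assessments will be blinded to group allocation". Under Control group, participants with Down syndrome in that arm do not join sessions or meet their student partner until the 8-week follow-up is done.

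Statistical analysis adjusts for the baseline score, age, sex and education level. Potential strengths and limitations concedes that "blinding of participants to their group allocation (intervention or control) is not feasible", but mentions neither the assessors nor the difference in collection route.

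**The concern.** An interviewer who speaks to a participant as a reading session closes knows that this participant is in the intervention arm. An interviewer who telephones for the 8-week assessment knows that the participant is a control. The procedure reveals allocation for every participant, so a stated safeguard is not in place where it matters most.

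The two routes also differ in setting and moment. One interview follows directly on games, shared reading and a reflection period. The other has no such context and is tied to week 8 rather than to a session. PedsQL taken by interview is a subjective measure, and participants cannot be blinded, so assessor blinding was the main protection left at data collection.

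Everyone is offered the intervention after T1, which makes T1 the only randomised comparison of the primary outcome. The article also intends to use the pilot's effect size to plan a definitive trial (Addressing gaps in literature), so a distorted estimate would carry forward.

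**Working it through.** The protocol gives no figure to reproduce here: no alpha, power, SD or effect size. The check is first one of logic. The arithmetic after it is illustrative.

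**Step 1. Does the procedure disclose the arm?**

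| | Intervention, T1 | Control, T1 |
|---|---|---|
| Route (Outcome measures) | researcher interview | researcher telephone interview |
| Moment | end of final session | 8 weeks, no session |
| Sessions attended by then | weekly sessions | none (Control group) |

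No cell is shared between the arms, so route identifies arm without error. Using separate interviewers for each arm would not help: each would still know the arm, and interviewer would become a further difference between arms.

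**Step 2. Can the analysis separate the two?** Let A be the arm (0 or 1) and M the collection route (0 or 1). By design M = A for every T1 record, so

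E[difference between arms] = treatment effect + route effect.

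A model term for M would duplicate A and could not be estimated. Adjusting for the baseline score does not remove the route effect, because it arises at T1. A blinded analyst does not undo it either.

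**Step 3. How much could it matter?** Assume no true effect and a route effect of b SD, and take an unadjusted two-sample t-test at two-sided 5%. With n per arm, the degrees of freedom are 2n − 2, the noncentrality is b·√(n/2), and

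rejection rate = P(|T| > t critical), with T noncentral t.

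The article's target is 12 dyads with 12 per group in brackets. That can be read as 6 or 12 per arm, so both are shown. The critical values are 2.228 (10 df) and 2.074 (22 df).

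| Assumed b (SD) | Noncentrality, n = 6 | Rejection, n = 6 | Noncentrality, n = 12 | Rejection, n = 12 |
|---|---|---|---|---|
| 0 | 0 | 5.0% | 0 | 5.0% |
| 0.2 | 0.346 | 6.1% | 0.490 | 7.6% |
| 0.3 | 0.520 | 7.6% | 0.735 | 10.8% |
| 0.5 | 0.866 | 12.3% | 1.225 | 21.6% |

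Coverage of the 95% interval for the true (zero) effect is one minus these rates: for example, 78.4% at 12 per arm with b = 0.5.

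**Step 4. Effect on the next trial.** Per-arm size for 80% power at two-sided 5% is 2(1.960 + 0.842)²/d² = 15.70/d². Assume a true effect of 0.3 SD and a route effect of +0.2 SD:

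- Sized on the contaminated 0.5 SD: 15.70/0.25 = 62.8, so 63 per arm.
- Sized on the true 0.3 SD: 15.70/0.09 = 174.4, so 175 per arm.

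The definitive trial would be planned at a little over a third of the size it needs (63/175 = 0.36).

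**The case against.** This is a pilot that expects it may not reach significance and promises cautious interpretation, so a false-positive rate is not the main harm. On the same unadjusted basis the 95% interval has a half-width of 2.074·√(2/12) = 0.85 SD at 12 per arm and 2.228·√(2/6) = 1.29 SD at 6 per arm. The assumed shifts lie well inside that. The planned analysis is a baseline-adjusted mixed model, not a t-test. All of this is fair, and it makes the rejection rates illustrative only. It does not remove the bias, and imprecision is no defence when the estimate is meant to size a later trial.

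The direction is also unknown. A pleasant session could raise scores, but tiredness after it could lower them. That stands. Nor does the article say who is present at either interview, and that the session-end interview is face to face is inferred from the in-person activities described under Shared book reading intervention.

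The blinding statement is not wrong throughout. Baseline assessment precedes allocation, students complete an online survey in both arms, and the later follow-ups belong to a single-arm phase. The failure is confined to the T1 interviews of participants with Down syndrome.

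Finally, the sentence calling the other measurements identical may refer to instruments rather than to how they are administered. That reading is reasonable, so the case does not rest on that sentence.

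**Conclusion.** The concern holds. For the T1 interviews of participants with Down syndrome, the collection procedure contradicts the stated blinding of follow-up assessors. Mode, setting and timing coincide with arm in the only randomised comparison of the primary outcome, and nothing in the analysis or the limitations section repairs this. These conclusions follow from the article's own text and need no assumption.

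The size does rest on assumptions. A route effect of 0.2 to 0.5 SD with no true effect would lift a nominal 5% error rate to between 7.6% and 21.6% at 12 per arm, or between 6.1% and 12.3% at 6 per arm. The document establishes neither the size nor the sign of the route effect. As written, the primary estimate cannot be read as a treatment effect alone, so this should be corrected before T1 data are collected.

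**What to change.** Replace the two arm-specific sentences under Outcome measures with one rule for both arms:

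- The T1 PedsQL interview uses the same mode, setting and time window in both arms: for example, by telephone within a fixed window around week 8 after randomisation, and never on a session day.
- The interviewer does not attend reading sessions, and families are asked beforehand not to reveal the arm.
- The friendship questionnaire, which only intervention dyads complete at T1, is given separately, after the PedsQL interview or by another person. Otherwise it would reveal the arm.
- If some participants cannot manage the chosen mode, the alternative is offered on the same criteria in both arms.

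Using the same mode at baseline is sensible for comparability, but no arm difference is documented there.

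If the routes cannot be aligned, restrict the blinding statement so that it no longer covers the T1 interviews (the baseline part may stay), make clear that only the instruments are identical, and list the confounding of route with arm as a limitation. The pilot effect size should then not be used on its own to size the definitive trial.

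The cost is mainly protocol wording, since telephone interviewing is already planned for controls. The drawbacks are the lost convenience of collecting data at the session, the need to keep callers separate from session staff, and greater difficulty by telephone for participants with little speech. Caregiver support during assessments is already allowed.
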